**6. Proportion of mothers confident they can identify the best place for care for sick children (time frame: 3 months)**
This secondary outcome measures the proportion of mothers who feel confident in identifying the best place to seek care for their sick children based on the child’s health problems. During the baseline and endline surveys, participants will respond with “strongly agree,” “agree,” “unsure,” “disagree,” or “strongly disagree” to the following statement: “I am able to identify the best place to get care for my child when he/she is sick.” This outcome will be recorded as a binary variable: participants responding “strongly agree” or “agree” will be classified as confident, while those responding “unsure,” “disagree,” or “strongly disagree” will be classified as not confident.

### Statistical Analysis

We will use the STATA (StataCorp) statistical software package for all analyses. Descriptive statistics will first be used to assess differences between the intervention and control groups in terms of baseline characteristics and potential confounding variables. Missing covariates will be imputed as needed, and system use (including adherence to the intervention) will be measured through self-reports at endline. Differences between the intervention and control groups after the intervention will then be analyzed for both primary and secondary outcomes. Two-tailed *t* tests or ANOVA will be used for continuous variables, and chi-square tests will be used for binary outcome variables.

For our main analysis, differences between the 2 arms (participants who received provider information biweekly and those who received no information) will be assessed using regression models. Participants with missing outcome data will be excluded from the analysis, as we do not plan to impute outcomes. For missing baseline covariates, we will assume that the data are missing at random and conduct a complete-case analysis using only observations with complete data for the relevant variables. Additionally, we will perform multiple imputation to handle missing responses for baseline covariates.

Given that this is a randomized trial with individual-level randomization and a cross-sectional design, our primary analysis will compare outcomes between treatment arms using data measured at endline. Therefore, we do not anticipate issues related to clustering or intraindividual correlation in the analysis of primary outcome measures. Treatment effects for continuous outcomes will be estimated using linear regression with robust SEs to account for potential heteroskedasticity, using the following regression model:

*Y_i_* = *β*_0_ + *β*_1_*T_i_* + *e_i_*

where *Y_i_* is the outcome for individual *i*; *T_i_* is the indicator for the treatment group; *β*_0_ is the value of the control group; *β*_1_ is the estimated treatment effect; and *e_i_* is the error term. For binary outcomes, we will use the following regression model:

logit(*Y_i_*) = *β*_0_ + *β*_1_*T_i_* + *e_i_*

In secondary analyses, we will adjust for baseline covariates—including age, wealth status, educational level, ethnicity, and parental health literacy—to account for potential differences and address any imbalances between the treatment and control groups.

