### Sample Size Determination

The required sample size was calculated based on the proportion of mothers who changed providers for nonurgent care in a 6-week pilot study involving 58 participants. In the pilot, all participants received the intervention—a web page of facility ratings—once or twice, depending on when the endline survey was scheduled. A conservative sample size was calculated to detect a 12-percentage-point change in the outcome with 80% power and α=.05; 330 participants per group would be required. Assuming 10% attrition, the total required sample size was set at 660 participants.

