### Outcomes

Trial outcomes will be measured through the in-person endline survey. For the primary analysis, we will assess the proportion of mothers who changed their preferred health care facility for nonurgent child care services between the baseline and endline surveys. The null hypothesis is that there is no difference between the control and intervention groups. The alternative hypothesis is that there is a difference between the 2 groups. This hypothesis aligns with our study aims, as it examines whether the use of provider facility ratings influences caregivers to seek alternative sources of health care for their children. Our primary analysis is cross sectional; for the panel analysis using the care-seeking panel, observations will be clustered at the household level.

Nonurgent care is defined as a child presenting with a mild fever of 38°C accompanied by a cough. During the baseline and endline surveys, participants will be asked to specify their preferred location for child care using the following question: “If your child is sick tomorrow with a mild fever of 38°C Celsius and cough, which hospital, clinic, or health center would you take your child to?” The primary outcome will be a binary indicator reflecting whether participants changed their preferred location between baseline and endline.

We used the proportion of mothers who changed providers (n=26, 45%) for nonurgent care in a 6-week pilot study involving 58 participants. All participants in the pilot received the intervention—a web page of facility ratings. Eligible women will be randomly selected from the ongoing VITERBI study for enrollment, and recruitment will continue until we reach 660 participants, with 330 in each intervention arm, assuming 10% attrition. Enrolling 300 participants per intervention arm provides 90% power, with a 2-sided α of .05, to detect a 12-percentage-point change in health facility choice, assuming 80% follow-up. We will collect and analyze baseline and endline survey data from mothers enrolled in the study. We anticipate completing 600 endline surveys and analyzing this sample.

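### The main binary analysis is a valid but unadjusted logit: it leaves baseline precision unused, and its parameter is not the 12-point difference the trial was sized on

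*Protocol article*

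**What the plan says.** In the protocol article, Statistical Analysis gives regression as the main analysis. For binary outcomes it writes logit(Y_i) = β0 + β1·T_i + e_i, with the treatment indicator as the only regressor, and says that "our primary analysis will compare outcomes between treatment arms using data measured at endline". Adjustment comes later: "In secondary analyses, we will adjust for baseline covariates—including age, wealth status, educational level, ethnicity, and parental health literacy". Chi-square tests for binary outcomes are also planned.

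For missing baseline covariates, the same section first mentions imputation as needed, then plans to "conduct a complete-case analysis using only observations with complete data for the relevant variables", and then adds multiple imputation. It does not say which approach leads.

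The primary outcome (Outcomes section) is a binary indicator of whether the preferred facility differs between baseline and endline. Secondary outcomes 4 and 6 (Textbox 1) are asked at both surveys; for outcome 6, "During the baseline and endline surveys, participants will respond with" a five-level agreement scale. Their baseline values are not among the named adjustment covariates, and neither is baseline preferred facility.

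The design target is on the difference scale. Sample Size Determination says "A conservative sample size was calculated to detect a 12-percentage-point change in the outcome", and Outcomes repeats the 12 points "with a 2-sided α of .05, to detect a 12-percentage-point change in health facility choice". The only rate given is the pilot's 26 of 58 (45%), and every pilot participant received the intervention. No control-arm rate is stated.

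**The concern.** Two things are at stake.

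**Precision.** A mother's starting facility plausibly predicts whether she names a different one three months later. Her baseline answer to an item plausibly predicts her endline answer to it. These data are collected in any case. If they are prognostic, leaving them out of the main model makes the standard error larger than it need be.

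**Scale.** The fitted coefficient is a log odds ratio. Without a control rate, a reader cannot convert a reported odds ratio back to the planned 12 points. The secondary adjusted logit adds a further difficulty: its conditional odds ratio differs from the unadjusted one even when the effect in percentage points is identical, so the two can look discordant for purely mathematical reasons.

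**Working it through.** **Inputs from the article.** Two-sided α of .05; 1:1 allocation; a 12-point difference; 600 endline surveys expected (300 per arm); pilot rate 26/58 = 44.8%.

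**Assumptions.** The control rate is not given. The main case here is 33% v 45%, with other pairs shown. R2 for the baseline covariates is not given; the range used is 0 to 0.20.

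**1. The plan's own power figure.** With pooled variance under the null,

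power = Φ{ [d√n − 1.96·√(2·p̄·(1−p̄))] / √(p1(1−p1) + p2(1−p2)) }.

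For 33% v 45% and n = 300: d√n = 0.12 × 17.32 = 2.078; p̄ = 0.39, so 1.96·√0.4758 = 1.352; the denominator is √(0.2211 + 0.2475) = 0.6845. Then (2.078 − 1.352)/0.6845 = 1.061, and power = 85.6%. For 45% v 57% it is 83.8%. The article says "Enrolling 300 participants per intervention arm provides 90% power" in Outcomes, and "with 80% power and α=.05; 330 participants per group would be required" in Sample Size Determination. Neither pair that uses the pilot's 45% reproduces 90% (a lower pair, 21% v 33%, gives 91.4%). That is a separate sample-size matter; 85.6% serves here only as the unadjusted starting point.

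**2. What adjustment could add.** Use effective n = 300/(1 − R2) in the same formula; the standard error is multiplied by √(1 − R2).

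| Assumed R2 | Effective n per arm | SE factor | Power, 33% v 45% |
|---|---|---|---|
| 0 | 300 | 1.000 | 85.6% |
| 0.02 | 306 | 0.990 | 86.3% |
| 0.05 | 316 | 0.975 | 87.3% |
| 0.10 | 333 | 0.949 | 89.0% |
| 0.20 | 375 | 0.894 | 92.2% |

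The gains are 0.7, 1.7, 3.4 and 6.6 points. A simulation (2,000 runs, 300 per arm) of unadjusted against adjusted logits agrees in direction and size: 85.0% v 87.0% at R2 about 0.05, and 85.6% v 91.3% at about 0.16.

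**3. What 12 points means as an odds ratio.** OR = [p2/(1−p2)] / [p1/(1−p1)].

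- 10% v 22%: 0.2821/0.1111 = 2.54
- 20% v 32%: 0.4706/0.2500 = 1.88
- 33% v 45%: 0.8182/0.4925 = 1.66 (risk ratio 0.45/0.33 = 1.36)
- 45% v 57%: 1.3256/0.8182 = 1.62

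In the same simulation, with the marginal difference held at 12 points, the conditional odds ratio was 1.66 with no prognostic covariate, 1.71 at R2 about 0.05 and 1.84 at about 0.16.

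**4. Does the odds-ratio scale itself lose precision?** No. A logit with one binary regressor is saturated. Fitted to 99/300 v 135/300, it returns 33.0% and 45.0%, a difference of 12.0 points and a delta-method SE of 0.0395. The direct calculation gives the same: √(0.4686/300) = 0.0395.

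**The case against.** The strongest reply is that an unadjusted primary comparison with secondary adjustment is conventional and valid in an individually randomised trial. That stands: this is a choice about efficiency and reporting, and no bias or type I error problem follows from it.

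A reader might infer several stronger things that the article does not support.

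- **That baseline answers are ignored.** The primary outcome, and secondary outcomes 3 and 5, are built from a baseline and an endline answer. What is missing is adjustment for them. The covariate list is also introduced as illustrative, so baseline facility is unnamed rather than ruled out.
- **That interpretability is lost.** The article names no reported effect measure, frames the primary outcome as a proportion and plans chi-square tests. The difference can be recovered exactly from the saturated logit (step 4). The reported measure may also be set in an analysis plan that is not shown.
- **That mothers with missing covariates are simply dropped.** Multiple imputation is planned alongside the complete-case analysis, and the unadjusted main model loses nobody to missing covariates. What stays open is which approach leads, and this matters once covariates enter the main model.
- **That the additive error term invalidates the model.** A logistic model for a 0/1 outcome has no such term, but this is a slip of notation that does not change what software would fit.

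It is also fair to object that the size of the gain rests on an R2 and a control rate the article does not give, and that changing the primary model of an open-label trial already under way has a cost. Both objections stand.

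**Conclusion.** The point holds as an improvement to a valid plan. The main model is fixed as unadjusted, although potentially prognostic baseline data are collected, and its parameter is on a different scale from the design target.

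With 300 analysed per arm and an assumed 33% v 45%, adjustment would be worth under 2 points of power for R2 up to 0.05, about 3 points at 0.10 and 6 to 7 points at 0.20. Nothing in the article shows where in that range the covariates fall. The precision gain comes only from the covariates; moving from an odds ratio to a risk difference adds none, but aligns the reported effect with the 12-point target.

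It would be tempting to attribute the gap between 85.6% and the stated 90% to this choice. The article does not support that: the gap arises in the sample-size calculation before any choice of model, and should be judged there.

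**What to change.** By dated amendment, before the analysis:

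1. Make the main model for the primary outcome a logit for Pr(Y = 1), with no error term, on arm, baseline preferred-facility type (for example the four provider types in Textbox 1, measure 2) and the five listed covariates. Report the standardised risk difference with a 95% CI.
2. Add the baseline value of the same item for secondary outcomes 4 and 6, and baseline urgent-care facility type for outcome 5.
3. Make the already planned imputation of baseline covariates the lead approach, so that no mother with a known outcome is dropped. Complete-case analysis becomes a check.
4. Keep the unadjusted difference in proportions as a sensitivity analysis.

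The article places randomisation at enrolment and the baseline survey immediately after it. The amendment should therefore confirm that baseline answers were recorded before the mother and staff knew the arm.

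The cost is protocol wording and a few lines of Stata, with no new data. The real downside is a documented change of primary model in a trial already under way, where Limitations says complete blinding of the analyst is not possible. The amendment should state its date and reason, and that no outcome data by arm informed it.

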### Ethics Considerations

This study was conducted in accordance with the Declaration of Helsinki and received ethics approval from the Ethikkommission Nordwest- und Zentralschweiz in Switzerland (approval ID AO_2023-00063) on September 8, 2023, and from the National Ethics Committee for Health Research (NECHR) in Lao PDR on February 6, 2024 (No. 16/NECHR). The research will adhere to the principles of the Helsinki Declaration, and any secondary use of the study data will undergo new ethical approvals.

All study participants provided informed written consent before taking part in any study procedures. They were informed that participation was voluntary, that they could withdraw at any time, and that withdrawal of consent would not affect their subsequent medical assistance or treatment. No financial compensation was provided for participation; however, a small gift of appreciation was offered upon successful completion of the endline survey.

The project included several steps to safeguard data privacy. First, deidentified survey responses (baseline, endline, and mobile) were stored on password-protected servers. Second, WhatsApp was used only as a communication channel with participants and not for any data collection purposes. Communication was managed by dedicated staff using a unique WhatsApp profile created specifically for the study. All exchanges via WhatsApp were protected by the platform’s default end-to-end encryption. Finally, to further minimize risks, WhatsApp records were deleted once participants had completed the endline survey.

## Results

The trial is currently in progress and is expected to be completed in 2025. From the results, we aim to determine whether web-based reviews of health care providers can influence mothers’ care-seeking behavior for their children in Vientiane, an urban setting in Lao PDR. Additionally, we aim to validate a scalable model for generating demand for high-quality care in urban, low-resource settings with high mobile phone coverage. Findings will be disseminated through local seminars, international conferences, and peer-reviewed journals.

## Discussion

### Anticipated Findings

This protocol describes a randomized controlled trial designed to test whether a demand-side intervention influences health facility choices among mothers in Vientiane capital. We will assess whether information about the quality of health care facilities—generated by study participants during the pilot and study periods—encourages mothers to change their preferred providers for nonurgent conditions. Additionally, we will assess whether the intervention leads to higher satisfaction with care at the most recently used facility and test our theory of change that mothers in the treatment group are more confident in their ability to identify the best place to seek care for sick children.

This protocol has several key strengths. It will contribute to the literature on how to “ignite demand” for high-quality care, as called for by the Lancet Commission on High-Quality Health Systems. This study is among the first published efforts to generate demand for high-quality care, providing evidence on how users of the health system can influence its quality. The results will apply to health conditions beyond the focus of this study—health care for children. The study is particularly relevant in Lao PDR, where the number of health care providers is rapidly growing, ranging from small primary health centers to large tertiary hospitals. The absence of effective gatekeeping allows people to seek care at any facility, including tertiary hospitals. Despite the growing care options, Laotians remain unsatisfied with the quality of care, with only 28% rating their usual health care provider as high quality. It is critical to understand and address sources of low-quality care, as low perceptions of care quality can lead people to forgo care or not adhere to medical advice [18].

A recent study highlighted that facility selection is influenced by factors such as illness severity, distance, technical skills and respectfulness of health care providers, cost, availability of equipment and medicines, waiting times, and informal payments [19]. Many of these factors, however, are not readily accessible or comparable across facilities, despite persistent dissatisfaction with care quality and untapped options. This study seeks to change the status quo by empowering patients with comparable information on health care quality across multiple facilities.

Through online ratings of health care facilities for children, we aim to study whether access to information about providers influences caregivers’ choice of facility—measured by switching behavior—as an indicator of improved access to quality health care. We will also assess whether this information affects caregivers’ satisfaction with the health services received for their child or children. Drawing on findings from previous studies [2,19], the website presents user ratings across quality domains valued by residents of Vientiane, including provider skills, respectfulness, cost, availability of equipment, waiting time, cleanliness, and helpfulness of support staff.

As one of the first studies of its kind in a low-resource context, we aim to evaluate the online platform’s perceived usefulness, gather participant feedback, and measure engagement metrics such as page views and reported use of the website. In addition, we will assess whether the website increased caregivers’ confidence in selecting a health care provider for their children.

While empowering patients with information to make informed care choices, the intervention could also have unintended consequences. For example, demand for tertiary hospitals—already burdened with long waiting times—might increase, as they are generally perceived to provide the highest quality care. This effect may not apply to all types of illnesses, particularly those that can be easily diagnosed and treated at smaller facilities. Additionally, private care providers could attract patients by improving observable aspects of care without addressing underlying gaps in technical quality.

Despite potential unintended consequences, our study offers a demand-side approach to addressing low satisfaction with care quality by empowering patients with actionable quality metrics. We aim to validate a scalable model for “igniting” demand for high-quality care in low-resource settings by establishing an accountability mechanism that links provider performance with patient preferences.

### Limitations

This protocol also has some limitations. First, the study may inadvertently encourage bypassing of lower-level public health facilities, directing mothers toward specialty hospitals or private providers. A recent study showed that a large majority (64%) of people used public hospitals as their preferred health care provider, while only 13% used health centers [20]. As a consequence of the study, government-managed specialty hospitals and private facilities may experience increased demand for services for minor health conditions that could be better managed at lower-level government facilities. This shift toward private and specialty providers could raise out-of-pocket expenditures for health care clients and increase costs for the health system as a whole. Second, the quality of care measures used in the study are based on participants’ perceptions and may be influenced by social desirability bias. However, previous studies have shown that people in Lao PDR are highly critical of health system performance [2,21]. Third, nonadherence to the intervention due to unexpected events—such as technical issues with the website or not receiving the URL—may also bias study findings. To address this, we will assess participants’ frequency of website use in the endline survey and document any website-related downtime. Fourth, because all participants reside in the same 2 districts and the study uses an open-label design, cross-arm exposure and spillover effects may bias the results. To minimize these risks, we have separated the roles of staff: the team member responsible for communicating with the intervention group (sending biweekly reminders and links to the ratings website) is not involved in scheduling or conducting endline surveys or other administrative assessment activities. Additionally, to assess aggregate exposure, we will track daily traffic to the website. To measure exposure at the individual level, all participants will be asked at endline about their knowledge of the intervention, whether they received the link, how they received it, and how frequently they accessed the website. Finally, the researcher responsible for data analysis will also be involved in data collection; therefore, complete blinding of the analyst is not possible. In practice, however, the analyst will remain blinded during the endline assessments.

